## Abstract

**Introduction:**

Knee osteoarthritis is a common disease with pain as the most prevalent symptom. Previous cohort studies have shown genicular artery embolization to reduce pain symptoms in patients with mild to moderate knee osteoarthritis. Patients resistant to conservative therapy but not eligible yet for surgical treatment due to young age or comorbidities may profit from an effective and sustained pain reduction treatment. This study is a randomized sham-controlled trial to evaluate the efficacy of genicular artery embolization in patients with knee osteoarthritis.

**Methods and analysis:**

Fifty-eight patients with mild-to-moderate knee osteoarthritis will be recruited and randomly allocated to the treatment or control group in a 1:1 ratio. Participants in the treatment group will undergo genicular artery embolization. Patients in the control group will undergo sham treatment. Outcome measurements will be assessed at baseline and after 1, 4, 8, and 12 months with questionnaires, pressure pain threshold testing, and MR imaging. The MR imaging protocol is designed to (semi)quantitatively assess osteoarthritis in the knee joint. The primary outcome is the change from baseline of the Knee injury and Osteoarthritis Outcome Score (KOOS) pain subscale after 4 months. Secondary outcomes include change in osteoarthritis-related questionnaires, pressure pain threshold, and OA-related MRI features, particularly synovitis and bone marrow lesions.

**Ethics and dissemination:**

This trial will determine the efficacy of genicular artery embolization compared to a sham treatment. This is of importance to assess before proceeding to larger-scale efficiency studies and, ultimately, implementing this treatment into day to day clinical practice.

**Trial registration:**

ClinicalTrials.gov NCT03884049. Registered on 21 March 2019

## Introduction

Knee osteoarthritis (OA) is the most common joint disorder and a leading cause of morbidity worldwide, ranking highly on the list of contributors to disability [1]. OA also induces substantial costs both directly through medical costs as well as indirectly through loss of work productivity [2]. The most common complaint is pain. At early stages, OA is treated with exercise, weight management and topical or oral non-steroidal anti-inflammatory drugs (NSAIDs), and add on therapy with a brace and/or intra articular corticosteroid injections [3]. End-stage knee OA is treated surgically with knee joint realignment, unicompartmental or total knee arthroplasty. However, not all patients resistant to conservative therapy are automatically eligible for surgical treatment due to young age or comorbidities. Furthermore, some patients choose to not undergo surgical treatment themselves despite increasing pain and limitation [4]. There are currently no effective alternative treatments for this group of patients. It is estimated that 3.6 million Americans belong to this group and this number is projected to increase to 5 million by 2025 [5].

Recent clinical studies have shown an effective pain reduction following genicular artery embolization treatment (GAE), during which periarticular angiogenesis is embolized [6–9]. The observed improvement of pain symptoms, combined with new insights in the pathophysiology of knee OA, offer an opportunity for a novel treatment beneficial to patients in the aforementioned treatment gap. Targeting angiogenesis, which is increased in among others the synovium and the osteochondral junction, potentially reduces pain symptoms [10]. This angiogenesis is thought to be associated with synovitis, osteochondral damage and osteophyte formation. It is also accompanied by nerve ingrowth, innervating tissues that are normally not innervated. Therefore, decreasing angiogenesis through GAE may potentially have a positive effect on symptomatic knee OA.

Okuno et al. used GAE to reduce angiogenesis in 95 patients with knee OA [7]. They found a significant reduction of pain symptoms measured by the Western Ontario and McMaster Universities Osteoarthritis Index (WOMAC) pain scores (0–20 scale) from 12.1 at baseline to 2.6 after 24 months. More recently, in a study of 20 patients, Bagla et al. found a significant reduction of the mean pain visual analog score (VAS) of 76 to 29 on a 0–100 scale [8]. Although these results show promise of GAE to bridge the treatment gap for a significant proportion of knee OA patients, these previous studies were both prospective non-randomized cohort studies. Hence, it is unknown how much of the observed effect is attributable to the placebo effect. It is well known that the placebo effect plays a major role in knee OA treatment and that the type of treatment is a determinant for the magnitude of the placebo effect, which has been shown to be larger for invasive treatments [11]. To rule out the placebo effect and determine the true efficacy of GAE, a randomized controlled trial with a sham control group is mandatory. Furthermore, to investigate changes induced by GAE and understand how angiogenesis is tied in with knee OA symptoms, imaging is warranted.

Therefore, the main objective is to assess whether genicular artery embolization for patients with symptomatic knee OA results in significant pain reduction after 4 months compared to sham treatment. A secondary aim is to obtain further insight into the role of angiogenesis in knee OA pathophysiology using advanced magnetic resonance imaging (MRI). A tertiary aim is to investigate whether pain sensitization is influenced by GAE using pressure point threshold testing.

## Methods and analysis

### Study design

This study is a single-center, double blind randomized sham controlled trial. It will be performed at the Erasmus MC, University Medical Center Rotterdam, the Netherlands.

### Study population and recruitment

This is a study with multi-center recruitment from orthopedic outpatient clinics of the Erasmus MC and hospitals in the region. Written informed consent will be obtained by a clinical researcher prior to enrollment in the trial. The study population consists of patients age ≥ 18 years with symptomatic, mild-to-moderate radiographic knee OA (Kellgren and Lawrence (KL) grade 1–3) [12] resistant to conservative therapy. In order to be eligible for participation, we defined the following in- and exclusion criteria:

#### Inclusion criteria

Age ≥ 18 yearsKnee pain for a duration of ≥ 6 monthsKnee pain (numeric rating scale ≥ 4 to ≤ 8) on at least half of the days in the preceding month at time of inclusionInsufficient response to conservative treatment for at least 6 monthsRadiographic knee osteoarthritis (KL grade 1–3)

#### Exclusion criteria

Contra-indications for MRI (e.g., metallic foreign bodies, etc.)Contra-indications for angiography (e.g., coagulopathy)Previous surgical treatment for knee osteoarthritis (e.g., high tibial osteotomy), excluding knee arthroscopyMusculoskeletal co-morbidity (e.g., rheumatoid arthritis or gout) potentially masking the effect of GAERenal insufficiency, determined with a blood sample test (GFR < 30 ml/min/1.73 m^2^)Known allergy to contrast agents;Known allergies to barium sulfate, 3-aminopropyltrialkoxysilane, polyphosphazeneWomen who are pregnant or lactatingIntermittent claudication of affected limbIntra-articular injections in the ipsilateral knee less than 6 months agoOn the waiting list for joint replacement surgeryAmitriptyline usageInsufficient command of the Dutch languageLegally incompetent adults

Participation in this trial is voluntary and patients can stop at any time without providing a reason. Patients withdrawn from the trial will be invited to fill in the questionnaires from home if they are not undergoing any other form of treatment for knee OA.

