### Co-interventions

Data on the usage of co-interventions will be collected at every follow-up visit through an interview. Patients will be encouraged not to start any new conservative treatments they were not receiving at baseline. Besides no new pharmacological treatment, this also includes no new corticosteroid injections, physiotherapy, or the usage of a brace. They can, however, increase or decrease any pharmacological treatment they were receiving based on their complaints, continue an already ongoing physiotherapy treatment, or keep wearing a brace if they were using one. This information will be recorded.

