### Sample size calculation

Calculations are partly based on the previous observational studies by Okuno et al. [6, 7]. Despite a possible placebo effect, which account for effect sizes up to 0.5 [21], they found effect sizes of > 5. For our study, we assumed we would require to demonstrate a large effect size of > 0.8 (strong effect) compared to sham embolization since GAE still is (minimally) invasive. Assuming this projected effect size of 0.8, and a standard deviation of 16 for the KOOS (100-0) pain score (estimated from multiple OA studies at Erasmus MC), beta of 0.80, and alpha of 0.05, 48 patients (*n* = 24 per study arm) are required to detect an increase (higher scores indicate less pain) in primary outcome measure of 8 points in the control group (placebo effect) compared to 21 points in the intervention group. The targeted sample size will be 58 to account for approximately 20% of patients lost to follow-up. We also expect a more homogeneous study population since all included subjects have an NRS pain score ≥ 4 and ≤ 8. With this sample size, and in case of lower variation in pain scores than SD of 16, we expect we could also detect smaller effect sizes between 0.5 (moderate effect) and 0.8.

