### Statistical analysis

The primary outcome is the difference in KOOS pain subscale change from baseline to 4 months between both groups. Repeated measurements regression analysis for continuous variables will be performed, based on intention to treat analysis to determine a difference between groups. Generalized estimating equations (GEE) will be used to enable inclusion of all available measurements in the regression models even if they are correlated. It also allows us to adjust for unequal distribution of prognostic variables over the two groups, which easily can occur in smaller randomized clinical trials. Radiographic severity, pain pressure threshold, and degree of sensitized pain according to painDetect will all be tested for equal distribution and, if more than 10% different, we will test if this variable changes the estimate with more than 10%. If this is the case, the variable will be included in the adjusted analysis. The adjusted analysis will be the primary analysis, but we will also present the unadjusted analysis. If some of the patients do not receive the treatment as allocated, we will also perform a per protocol analysis where the patients that did not comply with the allocated treatment will be excluded. Repeated measurement regression analysis will also be used for all continuous secondary outcomes: KOOS subscales, VAS, ICOAP, painDETECT, EQ-5D-5L, and PPT scores.

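### Questionnaires stop for withdrawn patients who are on another knee-OA treatment, which conflicts with the intention-to-treat analysis and may leave informative gaps in the 4-month outcome

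*Protocol article*

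**What the plan says.** The rule stands at the end of the Exclusion criteria section of the protocol article: "Patients withdrawn from the trial will be invited to fill in the questionnaires from home if they are not undergoing any other form of treatment". The rest of the sentence limits this to treatment for knee OA.

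The Statistical analysis section defines the endpoint: "The primary outcome is the difference in KOOS pain subscale change from baseline to 4 months between both groups". It then sets the principle and the method: "Repeated measurements regression analysis for continuous variables will be performed, based on intention to treat analysis to determine a difference between groups", and "Generalized estimating equations (GEE) will be used to enable inclusion of all available measurements in the regression models even if they are correlated". A separate analysis is planned for another purpose: "If some of the patients do not receive the treatment as allocated, we will also perform a per protocol analysis".

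The Co-interventions section says: "Patients will be encouraged not to start any new conservative treatments they were not receiving at baseline". It has co-interventions recorded at each follow-up visit and does not make a new treatment a reason for withdrawal.

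The Sample size calculation section says: "The targeted sample size will be 58 to account for approximately 20% of patients lost to follow-up".

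**The concern.** Intention to treat compares all randomised patients as allocated, whatever happens to them later. That requires trying to measure the outcome in everyone who still agrees to be measured. Here the attempt depends on an event after randomisation, namely being on another knee-OA treatment. Patients enter with persistent pain and an insufficient response to conservative care, so those who leave and seek something else are plausibly those whose pain did not improve. Withdrawn patients who are not treated elsewhere are still asked for scores.

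If such departures are more frequent or more selective in one arm, the 4-month contrast is biased. The 8- and 12-month contrasts are more exposed, because there is more time to leave. Scores that were never requested cannot be obtained afterwards.

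The rule also fits poorly with the article's own handling of co-interventions. A patient who starts a treatment and stays in the trial is still measured, so the plan already accepts KOOS scores under other treatment.

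**Working it through.** **1. The plan's own figure.** Inputs from Sample size calculation: changes of 8 (sham) and 21 (GAE), so a difference of 13; SD 16; alpha 0.05, taken as two-sided; power 0.80. Per arm, n = 2 × (1.96 + 0.84)² × 16² / 13² = 23.8, rounded up to 24, or 48 in total. This matches. The target follows from 48 × 1.2 = 57.6, rounded to 58. The allowance covers lost numbers only; it gives no protection against selective loss.

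**2. Who is affected.**

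| Patient | 4-month score requested? |
|---|---|
| Stays in trial, no new treatment | Yes |
| Stays in trial, starts another treatment | Yes, treatment recorded |
| Withdraws earlier, no other treatment | Yes, from home |
| Withdraws earlier, on another treatment | No |

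Only the last row loses data, and only from withdrawal onward. Earlier visits stay in the GEE.

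**3. Size under assumed selective loss.** The article does not say how often this happens, so the loss rates are assumptions. If a fraction p of an arm is lost, and gap is the mean of those kept minus the mean of those lost, the kept mean exceeds the true mean by p × gap. Hence

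observed difference = 13 − (p_sham × gap_sham − p_GAE × gap_GAE).

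Changes are normal with the plan's means and SD, and P(lost) = f / (1 + exp(change/6)), with f = 0.25, 0.5 or 0.7. For f = 0.7, sham patients kept average 12.5 against −6.5 for those lost, so 0.236 × 19.0 = 4.5. GAE patients kept average 23.2 against −0.2, so 0.096 × 23.4 = 2.2. The observed difference is 13 − (4.5 − 2.2), about 10.8 from unrounded values.

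| Lost, sham/GAE | Observed (of 29 + 29) | Difference | SD after selection | Power | Power, same numbers lost at random |
|---|---|---|---|---|---|
| 8% / 3% | 27 / 28 | 12.4 | 15.7 | 0.82 | 0.84 |
| 17% / 7% | 24 / 27 | 11.6 | 15.2 | 0.76 | 0.81 |
| 24% / 10% | 22 / 26 | 10.8 | 14.6 | 0.70–0.71 | 0.78 |

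Power is for a two-sided two-sample t test at 0.05. The model attributes all loss to this one rule.

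**4. Whether GEE repairs it.** Large-sample check with separate means by arm and visit, visits at 1, 4, 8 and 12 months, an assumed within-patient correlation of 0.6, and a true difference of 13. Patients leave if the trigger score change is below −10, −5 or 0, which loses 13%, 21% or 31% of sham and 3%, 5% or 9–10% of GAE.

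- Leaving depends on the unseen 4-month value: the estimate is 10.1, 9.0 or 7.9 with independence working correlation, and 11.2, 10.5 or 9.7 with exchangeable.
- Leaving depends only on the observed 1-month value: 11.2, 10.6 or 9.9 with independence, and about 13.0 with a correctly specified exchangeable structure.

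**5. Direction.** With 20–30% lost from GAE and 10% from sham, and a correlation of 0.5–0.8 between leaving and outcome, the estimate rises to 14.2–16.9. With equal fractions and equal selection (10% or 20% in both arms) it stays at 13.

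**6. The benchmark.** The value 13 assumes that the other treatment does nothing. If it adds b points in those who take it, full follow-up gives 13 − b × (p_sham − p_GAE). At 24%/10%, b = 10 gives 13 − 10 × 0.14 = 11.6, and b = 15 gives 10.9.

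**The case against.** The strongest reply is that the rule reaches few people. It needs withdrawal and other treatment together, and nothing in the article links the two. Patients are blinded and the primary endpoint is at 4 months, so such departures may be rare; at 8%/3% the effect on the estimate and on power is small. This stands, and it limits the size of the problem. It does not remove the conflict between the two sections.

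A reader might infer stronger claims that the documents do not support:

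- **Treatment failures are removed from the analysis.** They are not. Failures who stay in the trial are followed, and the earlier visits of those who leave are kept.
- **No analysis could recover the missing values.** Step 4 shows that GEE can recover the contrast if leaving depends only on observed scores and the working correlation is right. Nothing ensures either condition.
- **The sham mean must be inflated, so GAE is disadvantaged.** That needs more selective loss from sham, which the article neither states nor implies.
- **The shortfall from 13 is the error of the rule.** Full follow-up would include scores under the other treatment and might itself give 11.6 or 10.9 (step 6), close to the 10.8 seen with the rule in place. What full follow-up then adds is mainly patients and precision.
- **Power falls to 0.62.** That figure pairs the reduced difference with the unselected SD of 16. Selection also lowers the SD, and the coherent figure is 0.70–0.71.

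The article is also a condensed text, so the lack of detailed missing-data methods or sensitivity analyses is no criticism. The point rests only on a collection rule that the article does state.

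**Conclusion.** The point holds in limited form. The follow-up rule for withdrawn patients conflicts with the intention-to-treat principle in the Statistical analysis section, because collection of the primary outcome depends on an event after randomisation that is plausibly related to that outcome. GEE on the available scores is a reliable remedy only if missingness is unrelated to outcome, or depends on observed scores alone with a correct working correlation.

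The size and direction of any bias are unknown. Across the assumed scenarios the 4-month estimate ranges from 7.9 to 16.9 around a planned 13, with no bias when loss and selection are equal in the two arms. These figures depend on loss rates, selection strength and a correlation that the article does not give. They show what could happen and do not predict this trial's result. The case for acting is that the lost scores cannot be recovered later and the remedy is cheap.

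**What to change.** Delete the condition on other treatment. Invite every withdrawn patient who still consents to data collection to complete the questionnaires from home at each remaining visit (1, 4, 8 and 12 months), whatever other treatment they receive. Record that treatment and its start date. Include these scores in the intention-to-treat analysis; a sensitivity analysis may handle scores after a new treatment differently. For any patient whose scores have already gone uncollected under the rule, report the number and timing by arm.

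The cost is one sentence in the protocol and a few more questionnaires through a home route that already exists. The planned sample size of 48, raised to 58, does not change. The downside is small: some scores will reflect the other treatment, so the intention-to-treat difference may itself fall below 13. The change concerns data collection only and leaves clinical care as it is.

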### Randomization, allocation concealment, and blinding

Patients will be randomized 1:1 using a random block size strategy with block sizes of 4 and 6. Randomization is performed using an online randomization tool (ALEA clinical: https://www.aleaclinical.eu/). The clinical researcher, blinded for randomization, will conduct the MRI scans, evaluate patients during follow-up, and will enter the patient data into an online database. The interventional radiologist who will perform the procedure will be automatically informed about the randomization result by email. The allocation will only be sent to the interventional radiologist and a third party within the department who safeguards the randomization code. All others, including the clinical researcher, treating orthopedic surgeon, and patients, will be blinded tot group allocation.

### Interventions

To ensure patients will be effectively blinded, several precautions are taken. The personnel in the intervention suite will be instructed not to mention the group the patient is allocated to or anything else that could compromise blinding status of participants. Patients will lie in supine position and wear a noise-canceling headphone with music to distract them from the procedure and surrounding sounds. The patient’s line of sight on the intervention working field and imaging monitors will be blocked by a surgical drape. The skin around the knee is cooled using ice packs to minimize non-target embolization to the skin vasculature. The groin area will be anaesthetized with 2% lidocaine 10 ml.

#### GAE procedure

Patients allocated to the treatment group will receive GAE treatment, performed by an interventional radiologist experienced in vascular embolization procedures.

Following local anesthesia, an antegrade 4 French (Fr) catheter will be inserted into the common femoral artery. Initial digital subtraction angiography targeted on the vessels around the knee will be performed using Iodixanol 320 mg I/ml (Visipaque 320, GE Healthcare, Chicago, IL, USA). Culprit vessels will be catheterized using a 1.8 Fr microcatheter with micro guidewire and embolized using Embozene Microspheres 75 μm or 100 μm (Varian Medical Systems, Palo Alto, CA, USA) dissolved in 20 ml of Visipaque 320 until stasis of flow is achieved. When no evident culprit vessel is identified, the distal branch of the genicular artery corresponding with the most painful location is embolized. After finishing the embolization procedure, the sheath will be removed, and the puncture location is manually compressed for at least 10 min after which patient is immobilized for at least 3 h, followed by discharge. The procedure time varies between 1 and 2 h.

#### Sham procedure

In the sham group, the patient setup is exactly the same as in the treatment group. After anesthesia, a small incision will be made mimicking the incision in the GAE group. The interventional radiologist will pretend to insert a catheter in the femoral artery and perform angiography and embolization. The common femoral artery will not be punctured. The C-arm of the angiography system and the table will be moved during the sham procedure mimicking the actual procedure; however, no images are actually made, so there is no unnecessary radiation exposure. The sham procedure will take approximately as long as the actual intervention.

After both procedures, the site of incision will be manually compressed for 10 min after which the patient is immobilized for at least 3 h followed by discharge. Before discharge, blinding for group allocation will be tested in all patients by asking in what group they think they were allocated to. They have 3 options: “intervention group,” “sham group,” and “I don’t know.” This timing has been chosen since testing later on in the trial could potentially be influenced by efficacy and side effects of the treatment [13].

